### Study procedures

#### Follow-up

Both cases and controls will require a single visit to their homes to administer the questionnaire and household survey and to carry out blood sampling and GPS mapping. This will occur within a 2-week period after the index case detection (see figure 2).

**Figure 2 BMJOPEN2014006004F2:**
[figure not shown]
Enrolment/study procedures flow chart.

#### Questionnaire

A standardised pretested questionnaire was developed with input from multiple relevant disciplines including public health, epidemiology, clinical, entomology, primatology and social science. The questionnaire will be administered to cases and controls by trained fieldworkers who are native speakers in Bahasa Malaysia or other local dialects. The questions will elicit possible associations of malaria with several categories of potential environmental, socioeconomic and clinical risk factors, particularly in the context of potential interaction with primate hosts and vectors. Owing to the nature of case and control recruitment it will not be possible to blind fieldworkers to the participant's recent malaria status. For children or younger participants who are either not able or are uncomfortable answering the questions, the household head or parent/guardian will be asked to answer from the participant's perspective. Participants who do not speak Bahasa Malaysia or other local dialects, or who are unable to answer the questions for other reasons, will have an appropriate family member answer for them.

#### Household survey

Fieldworkers will conduct a household survey to record data for a range of variables including household construction and utilities, malaria prevention methods used, ownership of assets, characteristics of the surrounding environment and other factors relating to potential monkey and vector exposure. All households will be mapped using a GPS receiver.

#### Economic status

An index of socioeconomic status will be derived using established methods.^55^
^56^ The index will incorporate locally validated surrogate markers of income including access to services (electricity, water, sanitation) and ownership of specific assets (motorbike, car, refrigerator, generator or television).

#### Blood sampling

Blood collection will be requested at time of enrolment for cases, controls and additional members of control households. A venepuncture or finger-prick will be performed for cases and members of control households, respectively. No additional blood will be collected from cases already enrolled in parallel clinical studies (which include all assays required for the case–control study). Whole blood will be used for preparation of Giemsa stained thin and thick blood films to assess for malarial parasites, and also collected using 3 ×20 µL spots on filter paper (3MM; Whatman, UK) and a 500 µL EDTA tube (Becton-Dickinson, New Jersey, USA). PCR will be performed using previously described methods for *P. knowlesi*^57^ and *P. falciparum*, *P. vivax*, *P. ovale* and *P. malariae*^58^ detection. Haemoglobin will be assessed using a portable spectrophotometer (HemoCue AB, Angelholm, Sweden) for controls or using standard hospital laboratory methods for cases. Testing for red blood cell polymorphisms potentially associated with *P. knowlesi* acquisition will be performed including glucose-6-phosphate dehydrogenase (G6PD) deficiency, Duffy antigen receptor for chemokines (DARC) and α and β thalaessemia. Blood on filter paper spots will be stored for potential future serological analysis of historical changes in exposure to *P. knowlesi* infection, as has previously been done for other *Plasmodium* spp.^59^

### Statistical plan

#### Primary

The exposures of interest to be compared between *P. knowlesi* malaria cases (PCR-confirmed monoinfection) and controls will include variables relating to demographic, behavioural and socioeconomic factors, red blood cell polymorphisms and serological and immunological blood markers. Analysis will be per protocol, with ORs (including 95% CIs) for exposure risk between cases with *P. knowlesi* infection and controls calculated by the Mantel-Haenszel method and then compared. Confounding variables will be adjusted for using conditional multiple logistic regression models. Normally and non-normally distributed numerical variables will be analysed using t tests and Mann-Whitney U tests, respectively. An initial analysis will be conducted for cases and matched controls with complete variable data sets. The extent of missing data will be assessed and the sensitivity of results to alternative approaches to imputing missing data will be explored, if considered necessary.

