## Aim and objectives

The study design described in this protocol will allow evaluation of the primary research question: “Which factors lead to increased risk of acquiring human *P. knowlesi* malaria in Sabah, Malaysia?” Secondary objectives will include comparisons of malaria acquisition risk between different *Plasmodium* spp, risk of severe disease within the *P. knowlesi* group of malaria cases, and evaluation of *P. knowlesi* clustering.

Information resulting from this study will assist in guiding public health strategies for malaria in this region and provide valuable human epidemiological data for integration with concurrent studies on the entomology, primatology and land use aspects of *P. knowlesi* transmission (Monkeybar project: UK MRC ESEI Grant #G1100796) and the clinical treatment of *P. knowlesi* malaria (clinicaltrials.gov #NCT01708876).

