#### Definition and selection of cases

All male or female patients of any age presenting to a study site with confirmed malaria.

*Inclusion criteria:* Positive microscopy for *Plasmodium* infection; documented fever or history of fever in the past 48 h; primarily resided in the study area in the previous 3 weeks; residence can be located and mapped; appropriate informed consent obtained.

*Exclusion criteria:* Previously enrolled as a case (repeat malaria infection); age <4 weeks; subsequent PCR negative for *Plasmodium* spp monoinfection.

Cases will be classified according to PCR confirmation of *Plasmodium* spp monoinfection. Severe and non-severe *P. knowlesi* cases will be defined by whether they meet modified WHO 2010 severe malaria clinical and laboratory criteria as described elsewhere.^17^

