#### Definition and selection of community controls

A systematic selection procedure will be used to recruit three community controls for each case matched to the same village. This number of controls was chosen to provide sufficient statistical power to measure exposure effects, while at the same time making the recruitment process feasible logistically. Selection of control households and individuals within these households will be conducted using a validated and pretested random method based on up-to-date Malaysian Public Health Department village maps and household lists. Corroboration of the number of households will be undertaken with local residents, public health officers and village heads, where available. Households will be numbered using either the map and/or the household head of family name. A smartphone application generates a random number corresponding to one of the households. Individuals primarily residing within the selected household in the previous 3 weeks will be numbered and then randomised by the same application. All households within the village and all individuals within that household will have an equal chance of being selected. If the selected individual is not present when the fieldworkers visit the household, then they will return up to three times, which may include an arranged later time on the same day or on subsequent days. This will minimise selection bias related to the higher likelihood of male adults or school age children not being present at the household during the day. If it is not possible to obtain informed consent from a selected individual or if the specified inclusion criteria are not met, another individual within the same house will be selected based on the next randomly generated number. Failing this an alternative household will be selected using the same method.

*Control inclusion criteria:* Appropriate informed consent obtained; agree to finger-prick blood sample; negative blood slide and PCR result for malaria (delayed); primarily resided in the study area in preceding 3 weeks; residence can be located and mapped; no history of fever in previous 48 h.

*Control exclusion criteria:* Previously recruited as a case; previously recruited as a control; member of a previously selected control household; age<4 weeks.

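### Serological and immunological blood markers are listed as primary exposures although case blood is drawn after infection, so for any marker that responds to infection the case-control odds ratio cannot be read as acquisition risk

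*Protocol article*

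**What the plan says.** The Aim and objectives section poses the primary question as "Which factors lead to increased risk of acquiring human" *P. knowlesi* malaria in Sabah. Under Statistical plan, Primary, the factors to be compared between PCR-confirmed cases and controls include demographic, behavioural and socioeconomic variables together with "red blood cell polymorphisms and serological and immunological blood markers". Mantel-Haenszel odds ratios are planned, with confounders adjusted for by conditional logistic regression.

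On timing, Blood sampling says: "Blood collection will be requested at time of enrolment for cases, controls and additional members of control households". Follow-up includes blood sampling in the home visit and says of that visit: "This will occur within a 2-week period after the index case detection".

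On the state of the participants, cases need positive microscopy and "documented fever or history of fever in the past 48 h". Controls need a negative slide and PCR and "no history of fever in previous 48 h". Under Exclusion/censoring, a control found positive on film or PCR is censored.

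Blood sampling also gives serology a different role: "Blood on filter paper spots will be stored for potential future serological analysis of historical changes in exposure to" *P. knowlesi* infection.

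**The concern.** A factor that leads to acquisition must precede infection. Red-cell polymorphisms do, because they are inherited. A serological or immunological marker measured in a person who already has malaria may partly reflect that malaria. The primary list puts both kinds side by side as exposures and makes no distinction between them.

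What is at stake is the odds ratio of each such marker. A consequence of infection could be reported as a risk factor for it, or a protective marker could appear harmful, in a study whose results are meant to guide public health strategy. Conditional regression on confounders does not help: the problem is not a common cause of marker and disease but the effect of the disease on the marker.

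**Working it through.** The article states no figure for these markers, so there is none to reproduce. The check has two parts.

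**1. Order of events, from the article**

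- Cases are sampled at enrolment (Blood sampling) or at a home visit up to 2 weeks after detection (Follow-up). Both follow infection.
- The section on matching for preceding time exposure puts the prepatent period at around 9–12 days. On that figure a case has been infected for more than a week by the time parasites are detected.
- Controls are uninfected and without recent fever by their inclusion criteria, and any later found positive are censored.
- No pre-infection sample is described. Nothing in the Primary section limits the comparison to markers that are stable in acute infection, or calls it descriptive.

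Current infection therefore separates the two groups at sampling by design.

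**2. Illustration of size, from assumed inputs**

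Let *p* be marker prevalence in controls and, under a true odds ratio of 1, in cases before infection. Let *c* be the share of marker-negative cases that the infection has turned positive by sampling. Neither is in the article. Then:

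- case prevalence = *p* + (1 − *p*)*c*
- apparent OR = [*p* + (1 − *p*)*c*] / [*p*(1 − *c*)]

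This exceeds 1 for every *c* > 0. Examples:

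- *p* = 0.5, *c* = 0.1: case prevalence 0.55; OR = 0.55 / 0.45 = 1.22
- *p* = 0.1, *c* = 0.6: case prevalence 0.64; OR = 0.64 / 0.04 = 16

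| Prevalence in controls | *c* = 10% | *c* = 25% | *c* = 50% | *c* = 60% |
|---|---|---|---|---|
| 10% | 2.11 | 4.33 | 11.0 | 16.0 |
| 30% | 1.37 | 2.11 | 4.33 | 6.00 |
| 50% | 1.22 | 1.67 | 3.00 | 4.00 |

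At *c* = 5% the three rows give 1.53, 1.18 and 1.11.

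The chance of a two-sided 5% significant result was computed for 210 cases (the article's stated minimum) and 3 × 210 = 630 controls, as an unmatched comparison of two proportions:

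- *c* = 10%: about 90%, 47% and 24% at prevalences of 10%, 30% and 50%
- *c* = 25%: close to 100%, 99.5% and 89%

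The direction can also reverse. Take a protective marker with true OR 0.5 and 30% prevalence in controls. Case prevalence before infection is 0.5 × 0.3 / (0.7 + 0.5 × 0.3) = 0.176. With *c* = 10%, 25% and 50% the apparent OR is 0.81, 1.44 and 3.33.

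The calculation ignores the village matching and assumes that infection raises the marker. A marker that falls with infection would be biased the other way.

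**The case against.** The strongest reply is that no such assay is scheduled. Blood sampling commits to films, PCR, haemoglobin and red-cell polymorphisms. It makes serology potential future work on stored spots and names no immunological test. The article also condenses a fuller document, where marker choice and the handling of current infection may be set out. A marker chosen for historical exposure might be long-lived and little changed by the present infection. This stands as a limit on certainty and size. It does not remove these markers from the primary exposure list, which is a stated analysis choice and carries no restriction.

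Three stronger readings are tempting, and the article does not support them:

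- A reader might infer that the infection will certainly manufacture a risk factor. With no marker named and testing optional, the text shows only that the comparison is open to this for markers that respond to infection.
- A reader might infer that the odds ratios for forest exposure or occupation will be distorted because these markers sit in the adjusted model. The Primary section adjusts for confounding variables, and a consequence of infection is not a confounder. The plan does not say that these markers will be covariates, though it does not bar it. As written, the problem is confined to each marker's own odds ratio.
- A reader might infer that the Primary and Blood sampling sections flatly contradict each other. They can be read together if the stored spots are later tested. They do give serology different roles, which should be reconciled.

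Nor should one say that every case is febrile when sampled: a history of fever within 48 h is enough for inclusion, and the home visit may come up to two weeks after detection.

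**Conclusion.** The concern holds, limited to serological and immunological markers that respond to current infection. For those, the planned case-control odds ratio does not answer the acquisition question, and the planned adjustment cannot repair it. This conclusion rests on the article's own timing and eligibility rules, not on the illustration.

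The size cannot be determined from the article. The range of about 1.2 to 16 under a true odds ratio of 1 depends wholly on assumed prevalences of 10% to 50% and conversion of 10% to 60%; smaller conversion gives smaller bias. Conversion of 10% would often go undetected at the higher prevalences, while 25% would nearly always produce a significant result.

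**What to change.** In Statistical plan, Primary:

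- Remove infection-responsive serological and immunological markers from the primary exposure list, or restrict the list to markers shown not to change with acute infection.
- Keep the red-cell polymorphisms.
- Report case values of any other marker descriptively, not as evidence on acquisition risk.
- State that those markers are not to be used as covariates in the acquisition models.
- Align the text with Blood sampling, so that both sections give serology the same role.

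A separate serology model for past exposure in PCR-negative controls and household members is optional. It would be additional analysis work and is not needed to cure the problem.

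The required change is to analysis wording. It alters neither recruitment nor sampling and loses no blood samples. The downside is that no case-control odds ratio is reported for the markers removed, but that estimate could not have been interpreted as acquisition risk.

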While comparisons in *P. knowlesi* transmission patterns between Sabah and Sarawak remain difficult given broad definitions of forest and forest-edge exposure in previous studies, differences in more specific related factors may be impacting on the patterns of clustering of *P. knowlesi* cases. Initial studies from Sarawak had shown a higher prevalence of *P. knowlesi* malaria in adult males with occupational forest exposure, with no clustering of cases despite the fact that most people live in communal longhouses.^5^ Data from Sabah have also documented up to 78% of *P. knowlesi* cases are male^17^
^19^ while for female cases a bimodal age distribution was described, which may still indicate that risk of infection is predominantly linked to exposure activities.^19^ In addition, no relationship with occupation was seen when comparing *P. knowlesi* with *P. falciparum* cases.^17^
^19^ However, a study at Kudat at the north-western tip of Sabah showed clear differences to Sarawak with both a wide age distribution of cases and contemporaneous family clusters including children and town residents, suggesting peridomestic transmission is also occurring.^43^
*P. knowlesi* cases in Sabah have also been shown to demonstrate temporal clustering, with marked seasonality (p<0.001) associated with a peak of cases in May and 3–5 months post-high rainfall.^19^
^43^

Evidence of peridomestic transmission in Sabah raises the possibility of human-to-human transmission. To date, this is not evident from focused studies outside Sabah where macaque and human samples have been compared. These include the analysis of *P. knowlesi* CSP or MSP gene sequences in Sarawak and Peninsular Malaysia, and also in other countries including Singapore and Thailand, which all showed a large number of shared haplotypes that were similarly diverse in both hosts, supporting a zoonotic rather than exclusively human transmission mode.^10^
^32^
^44^
^45^ In addition, no evidence of ongoing human *P. knowlesi* transmission in areas without a macaque reservoir has been documented. However, in the absence of large-scale molecular studies comparing humans and macaques in this region, and given human-to-human transmission has been demonstrated under experimental conditions,^40^ the occurrence of natural human-to-human *P. knowlesi* transmission alongside monkey-to-human transmission remains possible.

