#### Recruitment/sample size

We aim to recruit all cases of confirmed malaria of any species or severity over the study duration from Kudat and Kota Murudu district hospitals. On the basis of current recruitment rates of around 10 malaria cases per month over the last year from both sites, we expect to enrol approximately 240 cases of *P. knowlesi* malaria and an additional 90 cases of malaria due to other species in the period December 2012 to December 2014. For the 330 malaria cases we will recruit 990 matched controls. A recruitment logbook will be kept for all screened cases and controls to document reasons for non-eligibility, which will be included in the analysis. With three controls per case, assuming probability of exposure among controls (Po) is 0.1, and the relative risk (RR) of acquiring *P. knowlesi* malaria in exposed subjects relative to unexposed subjects is 0.3, we will need to study a minimum of 210 *P. knowlesi* cases to be able to reject the null hypothesis that there is no difference between cases and controls (ie, relative risk=1), with 80% power and an α level of 0.05.^54^

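### Cases who share a household enter as separate matched sets, so ordinary 95% CIs for household-level exposures will be too narrow wherever this happens

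*Protocol article*

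**What the plan says.** All references are to the protocol article.

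- **Recruitment of cases.** Study design and Recruitment/sample size provide for enrolling all eligible cases, with 990 controls for 330 cases, so each case brings its own set of three. Under Definition and selection of cases, the only bar on repeats is at the level of the person: "Previously enrolled as a case (repeat malaria infection". Living with an earlier case does not exclude anyone.
- **Recruitment of controls.** Under Definition and selection of community controls, a candidate is excluded as a "member of a previously selected control household". A household limit therefore exists, but for controls only.
- **Evidence of clustering.** The introduction's section on current epidemiological understanding cites a study from Kudat that found "contemporaneous family clusters including children and town residents". Clustering of *P. knowlesi* cases is also a secondary objective.
- **Household exposures.** The Household survey section covers house construction, utilities, prevention methods, assets and surroundings. Economic status adds an index built from services and assets. The section on matching to the home village gives power for household as well as individual factors as a reason for the design.
- **Analysis.** Statistical plan, Primary, names Mantel-Haenszel odds ratios with 95% CIs, t tests and Mann-Whitney tests. For adjustment it says: "Confounding variables will be adjusted for using conditional multiple logistic regression models". It names no variance estimator and no handling of shared households.

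**The concern.** Two patients from one house have the same house walls, surroundings, bed-net provision and asset index. When each forms its own matched set, that one household's characteristics are counted twice on the case side. Conditioning on the set removes what a case has in common with its village controls. It does not remove the correlation between two sets whose cases share a house.

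The error runs in the anti-conservative direction: a chance feature of a few multi-case houses is more likely to be declared a risk factor than the nominal 5% level implies. Household and peri-domestic exposures are a design target here, and the results are meant to guide public health strategy. Exposures that are merely correlated within families, such as inherited red-cell polymorphisms or shared behaviours, are affected in the same direction but less strongly.

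**Working it through.** **The plan's own figure.** The protocol gives no figure for household clustering. Its one design calculation is in Recruitment/sample size: "With three controls per case, assuming probability of exposure among controls (Po) is 0.1", relative risk "in exposed subjects relative to unexposed subjects is 0.3", "with 80% power and an α level of 0.05", leading to "we will need to study a minimum of 210" cases. Two-sided two-proportion formulas at 1:3 give 152 cases (171 with continuity correction) if the relative risk is read as an odds ratio, and 140 (159) if it is applied directly to the exposure probability. A matched case-control formula with no exposure correlation within sets gives 144. At an odds ratio of 0.3, about 210 (210.8) is reached only with a correlation of 0.5, which is not printed. Nothing below depends on this figure.

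**Inputs.** M = 3 controls per case and about 240 *P. knowlesi* cases, both from Recruitment/sample size. The share f of cases living in households with m cases each is not given, so it is an assumption and is varied.

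**Correlation between sets.** Take a binary household-level exposure with prevalence p, and q = 1 − p. Near the null, a set's conditional-logistic score is M/(M+1) × (case value − mean of its controls).

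- Variance per set: pq × M/(M+1) = 0.75 pq.
- Covariance of two sets whose cases share a house, with separate controls: pq × (M/(M+1))² = 0.5625 pq.
- Correlation: 0.5625 / 0.75 = 0.75.

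**Variance inflation.** Deff = 1 + 0.75 × (Σm²/Σm − 1). With share f in households of m cases and the rest alone, this becomes 1 + 0.75 f(m − 1). The ratio of true to model SE is √Deff. Type I error is 2[1 − Φ(1.96/√Deff)].

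Example, 20% in pairs: Deff = 1 + 0.75 × 0.20 × 1 = 1.15; √1.15 = 1.072; 1.96/1.072 = 1.828; type I error 6.8%.

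**Check by simulation.** 240 sets at 1:3, 4,000 runs, odds ratio 1, exposure prevalence 0.3. The Monte Carlo standard error of a coverage near 95% is √(0.95 × 0.05/4000), about 0.3 percentage points.

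| Assumed clustering | Deff | True/model SE | Type I error | Coverage, model SE | Coverage, SE clustered on case household |
|---|---|---|---|---|---|
| None | 1.00 | 1.00 | 5.0% | 94.8% | 94.7% |
| 5% in pairs | 1.04 | 1.02 | 5.4% | not run | not run |
| 10% in pairs | 1.075 | 1.04 | 5.9% | 94.4% | 95.4% |
| 20% in pairs | 1.15 | 1.07 | 6.8% | 93.2% | 95.1% |
| 20% in threes | 1.30 | 1.14 | 8.6% | 91.9% | 94.7% |
| 30% in threes | 1.45 | 1.20 | 10.4% | 90.1% | 95.2% |

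At prevalence 0.1 the pattern is the same. Model-based coverage falls from 94.6% with no sharing to 89.5% with 30% in threes, while clustered coverage stays at about 94.2% to 94.7%.

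**The case against.** The strongest objection is that the article names no variance estimator at all. The quoted sentence is right for a matched design, and a clustered variance is the kind of detail that a full protocol or analysis plan might supply; neither is shown. A reader might infer that the protocol has decided to treat co-resident cases as independent. The text does not say so. What stands is narrower: the methods named, applied in their ordinary form, carry that assumption, and the recruitment rules and cited background give a specific reason to expect it to fail.

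The second objection is about size. No section gives the share of co-resident cases. The introduction also reports no clustering in Sarawak despite communal longhouses, and the abstract says clustering has not been systematically evaluated. For the primary comparison, both patients must be PCR-confirmed *P. knowlesi* monoinfections, which reduces the number of qualifying pairs. At 5% to 10% in pairs the effect is small. This objection stands in full, so the point has to be conditional.

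Three further inferences are tempting but unsupported:

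- **That clustering takes the study below its 210-case minimum.** That figure does not follow from the printed inputs, which give 140 to 171 two-sided, so no shortfall against it can be shown.
- **That the variance should be clustered on village.** The argument concerns shared case houses only. Nothing here shows residual dependence between sets at village level after conditioning, and the number of villages is not given.
- **That all primary odds ratios are affected alike.** The 0.75 correlation holds only for exposures identical within a house. Many listed exposures are measured on individuals.

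**Conclusion.** The point holds in conditional form. The design lets several *P. knowlesi* cases from one household enter as separate sets, and the ordinary standard errors of the named analyses ignore this. Wherever it happens, 95% CIs for household-level exposures will be too narrow. The model SE would be understated by a factor of about 1.04 with 10% of cases in pairs, 1.07 with 20% in pairs and 1.14 with 20% in threes. There is no effect if no household has two cases.

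These sizes rest on an assumed share of co-resident cases, an exposure identical for all members of a house, independent controls across sets, and model-based standard errors. The direction of the error does not depend on the assumed share; its importance does.

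**What to change.** Keep the conditional logistic models and add a sentence to Statistical plan, Primary:

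- Compute standard errors with a robust (sandwich) variance clustered on case household. Where Mantel-Haenszel CIs would otherwise be reported, use univariable conditional logistic regression with the same variance.
- Report how many *P. knowlesi* cases share a household, and how many there are per such household.
- For household-level exposures, add a sensitivity analysis that keeps only the first case per household and its controls.

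Point estimates from the main conditional models, recruitment and data collection do not change. Households are already located and mapped by GPS, so the cluster identifier should be available. The cost is slightly wider intervals where cases cluster; if few cases share a house, the results will hardly move.

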**Methods and analysis:**

A population-based case–control study will be conducted over a 2-year period at two adjacent districts in north-west Sabah, Malaysia. Confirmed malaria cases presenting to the district hospital sites meeting relevant inclusion criteria will be requested to enrol. Three community controls matched to the same village as the case will be selected randomly. Study procedures will include blood sampling and administration of household and individual questionnaires to evaluate potential exposure risks associated with acquisition of *P. knowlesi* malaria. Secondary outcomes will include differences in exposure variables between *P. knowlesi* and other *Plasmodium* spp, risk of severe *P. knowlesi* malaria, and evaluation of *P. knowlesi* case clustering. Primary analysis will be per protocol, with adjusted ORs for exposure risks between cases and controls calculated using conditional multiple logistic regression models.

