### Study design

This will be a population-based case–control study conducted in two adjacent districts: Kudat and Kota Marudu in the state of Sabah, Malaysian Borneo (figure 1). Within the study sites, all malaria cases, regardless of parasite species, meeting specified inclusion criteria will be enrolled at the corresponding district referral hospital over a 2-year period. Research fieldworkers will go to the village of the case within 2 weeks of focal case detection and randomly select three community controls who have primarily resided in the village for the past 3 weeks. This will enable matching of the controls with the case by the same geographical area (local village) and preceding minimum time period of exposure risk (3 weeks).

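### In the primary matched comparison, the tests named for numerical exposures ignore the 1:3 matching, so the unadjusted P values are conservative, power is lost and no odds ratio results

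*Protocol article*

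**What the plan says.** The design is individually matched. The protocol article, under Definition and selection of community controls, plans to "recruit three community controls for each case matched to the same village". Under Study design it adds: "This will enable matching of the controls with the case by the same geographical area (local village) and preceding minimum time period of exposure risk".

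Under Statistical plan, Primary, the comparison is introduced as "The exposures of interest to be compared between *P. knowlesi* malaria cases (PCR-confirmed monoinfection) and controls". Three methods follow:

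- Odds ratios with 95% CIs by the Mantel-Haenszel method.
- Adjustment: "Confounding variables will be adjusted for using conditional multiple logistic regression models".
- Numerical variables: "Normally and non-normally distributed numerical variables will be analysed using t tests and Mann-Whitney U tests, respectively".

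No paired, stratified or matched form of the last two tests is named. The Abstract describes the primary analysis as adjusted odds ratios "calculated using conditional multiple logistic regression models".

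**The concern.** The Mann-Whitney U test is a test for two independent samples. The t test is named without qualification, and a simple paired t test does not fit sets of one case and three controls. So one paragraph treats the data as matched for adjustment and as unmatched for the crude analysis of numerical variables.

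Numerical exposures matter in this study. Age was deliberately left unmatched so that it could be examined as a risk factor (Non-matching controls for age/gender). A socioeconomic index is to be built from services and assets (Economic status), and neighbours may partly share these. The section on matching to the home village defends the matching by the power it gives for individual and household factors. Unmatched tests forgo some of that power. They also report no odds ratio, so a numerical exposure and a categorised version of it would be summarised on different scales at the crude stage.

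**Working it through.** **Inputs.** The ratio of 1 case to 3 controls and the minimum of 210 cases come from the protocol ("we will need to study a minimum of 210 *P. knowlesi* cases"), as do 80% power and α = 0.05 (Recruitment/sample size). Two-sided testing is an assumption. The within-set correlation ρ is not in the document, so it is assumed and shown from 0 to 0.5.

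**The plan's own figure.** The protocol gives no power figure for a numerical exposure. Its 210 refers to a binary exposure (10% among controls, relative risk 0.3) and is used here only as a number of sets. It does not follow readily from its stated inputs: the usual matched case-control formula gives 144 cases with no exposure correlation and 163 at a correlation of 0.3. That is a separate matter, and the type I error and power figures below do not depend on the number of sets.

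**Variance.** Let the four members of a set have common variance σ² and pairwise correlation ρ. The case minus the mean of its three controls has variance

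σ²[1 + (1 + 2ρ)/3 − 2ρ] = (4/3)σ²(1 − ρ).

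The independent-samples test in effect uses (4/3)σ². Its standard error is therefore too large by a factor of 1/√(1 − ρ).

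**Consequences**, with 1.96 for α and 1.96 + 0.84 = 2.80 for 80% power:

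- True type I error = 2·P(Z > 1.96/√(1 − ρ)).
- Power of the independent test, where the within-set analysis has 80%, = P(Z > 1.96/√(1 − ρ) − 2.80).

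| ρ (assumed) | SE ratio | 1.96 × ratio | True type I error | Power against 80% within sets |
|---|---|---|---|---|
| 0 | 1.00 | 1.96 | 5.0% | 80% |
| 0.05 | 1.03 | 2.01 | 4.4% | 78.5% |
| 0.1 | 1.05 | 2.07 | 3.9% | 77% |
| 0.2 | 1.12 | 2.19 | 2.8% | 73% |
| 0.3 | 1.20 | 2.34 | 1.9% | 68% |
| 0.5 | 1.41 | 2.77 | 0.6% | 51% |

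If a 95% interval for the mean difference were reported from the t test, it would be too wide by the SE ratio.

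**Simulation**, 210 sets, 4,000 runs per setting, no true difference. At ρ = 0.2 the rejection rate was 0.029 for the t test, 0.031 for Mann-Whitney and 0.051 for the within-set analysis. At ρ = 0.3 the rates were 0.018, 0.016 and 0.042; at 0.5 they were 0.006, 0.006 and 0.047. This agrees with the formula and shows that Mann-Whitney behaves like the t test.

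**What the loss is measured against.** It is a loss relative to the matched analysis, not a fall below what unmatched data would give. Fix the true difference at the value with 80% power when ρ = 0, that is 2.80 × √((4/3)/210) = 0.223 SD. The independent test then has power Φ(0.84/√(1 − ρ)) and the within-set analysis Φ(2.80/√(1 − ρ) − 1.96): 83% and 88% at ρ = 0.2, 84% and 92% at 0.3, 88% and 98% at 0.5.

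**The case against.** The strongest reply is that the sentence is only the numerical counterpart of the crude Mantel-Haenszel step. The conditional models are not restricted to binary exposures, and the Abstract places the primary analysis in those models. This stands. A reader might infer that numerical exposures get nothing but unmatched tests, or that the headline results are invalid. The document supports neither: it does not bar numerical variables from the conditional models, and the adjusted odds ratios respect the matching. What remains is that the only method named specifically for numerical variables is unsuited to the design.

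A second reply is that the error is conservative and its size unknown. This also stands. At ρ of 0.05 or less the loss is negligible, and age may cluster little, since individuals are drawn at random within randomly chosen households. A reader might infer that real effects will certainly be missed, or that false positives arise. The first depends on an unstated ρ and on the crude test being the only one; the second runs the wrong way for positive ρ.

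Third, some examples would be poor ones. An exposure constant within a village cannot be estimated by conditional regression on village-matched sets either, and the protocol knowingly gives up comparisons between villages. Haemoglobin is not listed among the primary exposures; anaemia appears under Secondary as a burden associated with malaria.

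Fourth, the article is condensed and the form of the t test is not stated, so independence is an inference for that test. It is not an inference for Mann-Whitney U, and naming an ill-fitting test differs from leaving out detail.

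**Conclusion.** The point holds for the unadjusted analysis of numerical exposures in the primary case-control comparison. Those P values are conservative for any positive within-set correlation. The loss of power relative to a matched analysis is about 1.5 percentage points at ρ = 0.05, 7 at 0.2 and 29 at 0.5. The figures rest on an assumed ρ, equal variances, a common correlation within sets, complete 1:3 sets and two-sided testing. At ρ = 0 nothing is lost, but the lack of an odds ratio remains.

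The severity is moderate: the direction is conservative, the adjusted analysis already respects the matching, and the remedy is already in the plan. It would be wrong to extend the point to the secondary comparisons of *P. knowlesi* with other species and of severe with non-severe cases. These compare cases with cases and are not matched, so t and Mann-Whitney tests are suitable there.

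**What to change.** Under Statistical plan, Primary, replace the sentence on numerical variables with wording such as:

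> For the comparison of *P. knowlesi* cases with their matched controls, numerical exposures will be analysed, unadjusted and adjusted, by conditional logistic regression stratified on matched set and reported as OR (95% CI) per stated unit. Skewed variables will be transformed or categorised. Means or medians will be given as description.

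Under Secondary, where a similar approach to the primary one is now invoked, state that t tests and Mann-Whitney U tests will be used for the unmatched case-case comparisons. Otherwise the new wording could be carried over to comparisons that have only one case in each matched set and so no contrast within sets.

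The cost is a sentence in each place. The models are already planned, and no new data or change to recruitment is needed.
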